### Schedule of activities

|                                            |                   |                                |
|--------------------------------------------|-------------------|--------------------------------|
| Step Identification                        | Beginning         | Term Screening of participants |
| Screening of participants                  | October 9, 2021   | March 3 , 2022                 |
| Double-blind and randomized phase          | April 01, 2022    | April 10, 2022                 |
| Open follow-up phase                       | May 15, 2023      |                                |
| Analysis of data from the randomized phase | July 08, 2024     | December 15 2024               |
| Open phase data analysis                   | February 10, 2024 | July 10, 2024                  |

We assure that the FIBRO-HB-tDCS study was initiated only after receiving approval from the CEP-CONEP (Ethical Review Board) System of the Hospital de Clínicas de Porto Alegre, the university hospital of the Federal University of Rio Grande do Sul (UFRGS), Porto Alegre, Brazil.

## Statistical Analysis

Continuous and categorical variables were compared using Fisher's exact test, the chi-square test, and the t-test for independent samples. The Shapiro-Wilk normality test was applied to determine the normal distribution of continuous variables. A Linear Mixed-Effects Regression Models for Repeated Measure (LMM) assessed primary outcomes (pain severity and disability) with treatment, placebo response (responder vs. non-responder), time, and the treatment-by-time interaction as fixed effects, and included a random intercept for patients to account for time differences. If appropriate, we then performed the Bonferroni's Test adjustment for post hoc multiple comparisons to identify differences between the groups at each time point and used a paired t test to assess the effects on each experimental group. The Generalized Linear Model (GLM) was used to examine the treatment effect on the secondary outcomes including quality of life, HPT, PGI-I and the descending pain inhibitory system (DPIS). The treatment effect on primary and secondary outcomes was adjusted for analgesic use and placebo susceptibility. Analgesic use was included in the model to control a potential confounder affecting pain outcomes. This ensures that the observed effects of a-tDCS and s-tDCS are attributable to the interventions rather than variations in analgesic use, thereby enhancing the validity of the results. All analyses were adjusted for multiple comparisons using Bonferroni's Test. The modified ITT (m-ITT) analysis included those completing  $\geq 50\%$  of sessions, with missing data imputed using regression model coefficients. In the m-ITT, with an adjusted protocol, encompassing all patients who completed at least ten sessions. The choice of ten sessions for ITT was guided by most of the literature supporting clinical symptom improvement in chronic pain. This method is not as strict as classical ITT, but it suggests that A-tDCS could be useful in clinical settings with at least a minimum number of sessions. Specifically, we replaced missing values with imputed data derived from a regression model using observed data. The treatment group served as the predictor, and the outcome variable with missing values was imputed based on regression coefficients, indicating the relationship between the treatment group and the outcome. This imputation method was applied, for example, to ten patients who withdrew after ten tDCS sessions. Sensitivity analyses confirmed consistent LMM results with or without imputation ([see per-protocol analysis in results - Supplement II](#)).

The standardized difference means (SDM) was used to compute the effect size (ES) by dividing the mean difference between a-tDCS and s-tDCS by the pooled baseline standard deviation (SD). The ES was interpreted as small if lower than 0.20 to 0.49, moderate if between 0.50 and 0.79, and large if larger than 0.80^54. All statistical analyses were performed using two-tailed tests at the 5% significance level with SPSS, version 22.0 (SPSS, Chicago, IL).

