**b. Objective**

To compare the effects of multisession (a-tDCS ) targeting the PFC, combined with exercise (E) and pain education (PEN), versus sham tDCS (s-tDCS ) on pain severity, daily activity interference (BPI), and pain-related disability (Br-PCP). Secondary outcomes included quality of life, heat pain threshold (HPT), changes in the Numerical Pain Scale (NPS 0-10) during the conditioned pain modulation test (CPM-test), Patient Global Impression of Improvement (PGI-I), and treatment adherence.

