## d. Objectives

This clinical trial aims to compare the efficacy of Multiple-session home-based self-applied anodal tDCS (a-tDCS) targeting the left dorsolateral prefrontal cortex (l-DLPFC) the long-term effects of combining exercise (E) and pain neuroeducation guidance (PNE), based on placebo-test responses (responders vs. non-responders) in the following outcomes:

**Primary outcome:** Brief Pain Inventory (BPI), which allows pain assessment from a multidimensional perspective (pain intensity and interference in general activities, mood, mobility, work, personal relationships, sleep and enjoyment of life, etc.) (primary outcome).

**Secondary outcomes:** To assess the effectiveness of multiple-session home-based self-applied anodal tDCS (a-tDCS) targeting the left dorsolateral prefrontal cortex (l-DLPFC) and the long-term effects of combining exercise (E) and pain education guidance (PNE), considering susceptibility to the placebo effect, on (1) the impact of pain on quality of life; (2) heat pain threshold; and (3) the function of the descending pain modulatory system. Additionally, the study aims to identify predictors of response to the placebo effect through a hierarchical model with an analytical structure defined a priori. This model will consider the hierarchical relationships between potential predictors, such as disability due to pain, catastrophizing, depressive symptoms, psychiatric diagnoses, level of central sensitization, baseline endorphin serum levels, current medications, and other relevant factors.

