### f.4. Sample size estimation

The primary outcome of this study, pain-related function, is measured using the 7-item Brief Pain Inventory (BPI) interference scale. This scale serves as a Multidimensional Pain Interference Index (MPII), providing a comprehensive view of how pain affects various dimensions of an individual's life, including emotional well-being, social interactions, and daily activities. Focusing solely on pain severity may fail to reflect the full impact of pain on a person's overall quality of life. The secondary outcome, pain intensity, is evaluated using the 2-item BPI severity scale. Both BPI scales range from 0 to 10, with higher scores representing worse function or intensity. Understanding the Minimal Clinically Important Differences (MCID) changes in pain interference scores is vital for clinicians to determine whether changes are significant enough to indicate meaningful improvements or declines in quality of life, rather than just being statistically significant. According to previous studies in chronic pain populations, an MCID of approximately 0.7 points for both the BPI interference and severity scales has been identified. However, consensus guidelines have established a 1-point difference as the MCID for both scales, while a 30% reduction from baseline is also recognized as a significant indicator of moderate improvement. In examining the effects of E-PNE with a-tDCS and s-tDCS groups at the final time point (moment 5), which occurs three months post-treatment, a more conservative MCID of 0.6 points was used for estimating the sample size. This cautious approach aims to ensure a thorough evaluation of the study's power to assess the treatment effects. The sample size estimation was performed using the PSS *Health tool* 32. [https://hcupa-unidade-bioestatistica.shinyapps.io/PSS\\_Health/](https://hcupa-unidade-bioestatistica.shinyapps.io/PSS_Health/). To detect a minimum difference of 0.6 points between the means of the Multidimensional Pain Interference Index (MPII) for the a-tDCS group and the s-tDCS group at the final time point (moment 5) in a repeated measures analysis, a sample size of 94 participants (47 per group) was calculated. To account for a potential dropout rate of 15%, the sample size was increased to 112 participants. This calculation was based on an

assumed 80% power, a 5% significance level, and relevant parameters for the treatment group.

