### **Primary Outcome**

- i. Pain interference was assessed using a multidimensional pain score from the Brief Pain Inventory (BPI), which evaluates seven daily activities: general activity, walking, work, mood, enjoyment of life, relationships, and sleep. BPI pain interference scores range from 0 to 10, with 0 indicating no interference and 10 indicating complete interference. Overall pain interference was calculated as the mean of the seven items. The assessment was conducted over a 4-week treatment period and at three months of follow-up .

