### **Secondary Outcomes:**

- ii. The Brief Pain Inventory (BPI) assesses pain at its “worst,” “least,” “average,” and “now” (current pain) on a 0–10 numerical rating scale, where 0 indicates no pain and 10 represents the worst pain imaginable. This assessment was conducted weekly during treatment and three months after treatment completion. These single-item measures are supported by IMMPACT recommendations for pain assessment in clinical trials  and the FDA Draft Guidance for Patient-Reported Outcome Measures .
- iii. The Brazilian Profile of Chronic Pain: Screen (B-PCP) identifies the individual's multidimensional pain experience across three domains: pain severity (0-32), disability (0-36), and emotional burden (0-25). Higher scores indicate

- greater disability or emotional distress, with a total score ranging from 0 to 93 points. Changes from baseline to the end of treatment and at three months follow-up will be analyzed.
- iv. Fibromyalgia Impact Questionnaire (QIF): Measures the impact of fibromyalgia on quality of life across three domains: function (9 questions), overall impact (2 questions), and symptoms (10 questions). Scores are weighted differently, with a maximum total score of 100 .
  - v. Patient Global Impression of Improvement (PGI-I): A 7-point scale assessing patients' perceptions of symptom improvement post-treatment, ranging from "very much worse" (1) to "very much improved" (7) . Impressions were categorized into "improved" or "very much improved" versus "very much worse" to "slightly improved".
  - vi. Quantitative Sensory Testing (QST) is a standardized protocol using a computer Peltier-based device thermode (measuring 30X30mm), which was attached to the skin on the ventral aspect of the mid-forearm. The temperature was set at 32OC and increased at a rate of 1 OC/s until it reached a maximum of 52Oc. Each participant was instructed to push the button when the stimulation became painful. To determine the heat pain threshold, each patient's threshold was measured three times, with a 40-second break between each assessment. The average of the three assessments was used to define the heat pain threshold for each patient .

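### The primary mixed model is assigned to pain severity and disability, but the trial defines and sizes its primary outcome as BPI pain interference

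*Protocol*

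**What the plan says.** All references are to the Protocol.

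- **f.4. Sample size estimation:** "The primary outcome of this study, pain-related function, is measured using the 7-item Brief Pain Inventory (BPI) interference scale". The same paragraph continues: "The secondary outcome, pain intensity, is evaluated using the 2-item BPI severity scale". The 0.6-point difference is set for the interference index at the final time point, moment 5, described as three months after treatment.
- **Primary Outcome:** interference is the only entry. "Overall pain interference was calculated as the mean of the seven items".
- **Secondary Outcomes:** these include the BPI pain ratings and the B-PCP, whose domains are "pain severity (0-32), disability (0-36), and emotional burden (0-25". For the B-PCP: "Changes from baseline to the end of treatment and at three months follow-up will be analyzed".
- **Statistical Analysis:** "A Linear Mixed-Effects Regression Models for Repeated Measure (LMM) assessed primary outcomes (pain severity and disability". A generalized linear model is then assigned to secondary outcomes, with quality of life, heat pain threshold, PGI-I and descending pain inhibition named. Interference appears in neither sentence. The section also states that Bonferroni adjustment was applied to all analyses, without saying whether this covers several primary outcomes.
- **b. Objective:** the comparison is "on pain severity, daily activity interference (BPI), and pain-related disability (Br-PCP", followed by a separate list of secondary outcomes.
- **d. Objectives:** the primary outcome is the BPI, described as allowing "pain assessment from a multidimensional perspective (pain intensity and interference in general activities" and further domains.
- **Schedule of assessment:** the BPI has a row; the B-PCP has none.

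**The concern.** The section that says which model decides the trial names two outcomes that the outcome sections call secondary, and omits the one they call primary. An analyst who followed it literally would run the decisive model on outcomes for which the sample size was not calculated, and would have no stated model for the outcome that was powered.

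Two outcomes called primary also raise the question of how the 5% is shared. The size calculation allows for one test at 5%. A reader of the results could not tell from this document which comparison was meant to carry the conclusion.

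**Working it through.** **Step 1: reproduce the plan's sample size.** Inputs from f.4 and its R code: difference 0.6, SD 1 in both arms, two-sided 5%, 80% power, 1:1 allocation, retention 100, 99, 98, 96 and 94%, and autoregressive correlation 0.4 (a-tDCS) and 0.2 (s-tDCS).

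The formula for a repeated-measures comparison at the last visit is n per arm = (φa + φb)(z₀.₉₇₅ + z₀.₈₀)² SD² / δ². Here φ is the last diagonal element of the inverse information matrix, given the correlation and retention pattern.

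- φa = 1.0597 and φb = 1.0629, sum 2.1226.
- n = 2.1226 × (1.9600 + 0.8416)² / 0.6² = 46.28, so 47 per arm and 94 in total. This matches.
- Dropout of 15%: 47 / 0.85 = 55.3, so 56 per arm and 112 in total. This matches.
- Power at 47 per arm: √(47 × 0.36 / 2.1226) = 2.823; Φ(2.823 − 1.960) = 80.6%.

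The size is right, and every input belongs to BPI interference.

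**Step 2: does it carry over to the outcomes in the analysis section?** For B-PCP disability (0-36) the protocol gives neither a target difference nor an SD, so 0.6 points with SD 1 on a 0-10 scale has no meaning there. For BPI severity it gives the same 0-10 range and the same MCIDs as for interference, but no SD and no calculation. Which severity measure is meant is also open: f.4 has a 2-item BPI scale, Secondary Outcomes has four single BPI ratings, and the B-PCP has its own severity domain (0-32).

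**Step 3: if two primary outcomes are kept.**

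- *Alpha not split.* The chance of at least one false positive is 1 − 0.95² = 9.75% for independent tests, and less if they are positively correlated.
- *Bonferroni covers them, 0.025 each.* With z₀.₉₈₇₅ = 2.2414, power per outcome at 47 per arm is Φ(2.823 − 2.241) = 72.0%. For 80%, n = 2.1226 × (2.2414 + 0.8416)² / 0.36 = 56.04, so 57 per arm and 114 evaluable. With 15% dropout, 114 / 0.85 = 134.1, about 135.

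Both power figures lend the interference assumptions (0.6, SD 1) to outcomes for which the protocol gives none.

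**Step 4: if interference alone is primary.** Nothing changes: 47 per arm, 112 enrolled, one test at 5%.

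**The case against.** The strongest defence is that *disability* in the analysis section is loose wording for interference. The sample size section calls interference pain-related function, the analysis section never names the B-PCP, and it assigns the mixed model to the primary outcomes, which are defined elsewhere. This is possible. Against it, section b. Objective ties interference to the BPI and disability to the Br-PCP in one sentence, and the B-PCP has its own disability domain. Even if the defence is granted, severity is still promoted from secondary to primary, and two primaries share a size built for one test.

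The 72% also has a limit. The formula already allows for 94% retention, so if all 112 enrolled followed that pattern, 56 per arm at 0.025 would give 80.0%. The margin added for 15% dropout would absorb the split, but only if that dropout did not occur.

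Four stronger readings are tempting, and the document does not support them:

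- *Three or four rival primaries, with a family-wise error of 14.3% for three.* Section b. Objective labels nothing primary, and d. Objectives is only less specific than f.4. The firm conflict is between Statistical Analysis and the two sections that define the primary outcome.
- *No multiplicity rule at all.* There is a general Bonferroni statement. Its scope is unclear, and detail may sit in an analysis plan not shown. That is why Step 3 gives both branches.
- *B-PCP was not collected.* The schedule is visibly incomplete (heat pain threshold has no row either), and Methods lists the B-PCP among the instruments used. A missing row is an inconsistency, not evidence of missing data.
- *The primary outcome was switched after the data were seen.* The section reports withdrawals and sensitivity results although the document is presented as the version submitted to the ethics committee in October 2021. That shows later text. It does not show which outcome was fixed first.

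**Conclusion.** The contradiction stands. The Statistical Analysis section assigns the primary model to pain severity and disability. The sample size and Primary Outcome sections make the 7-item BPI interference mean the sole primary, and severity and the B-PCP are secondary. Followed literally, the powered outcome is named in no planned model and the 80% power does not describe the outcomes called primary.

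Keeping two primaries means either a family-wise error of up to 9.75% (independence, no split) or power of about 72% per outcome (0.025 each, 47 per arm, interference assumptions borrowed). The sample size arithmetic is sound, and the defect lies in which outcome the analysis section attaches to it. It must be corrected, because it determines which test decides the trial.

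**What to change.** - In Statistical Analysis, name one primary test: BPI interference (mean of seven items), a-tDCS versus s-tDCS, at the final time point on which f.4 sizes the trial (moment 5, three months post-treatment). Give the time point by description as well as number, because the schedule lists six BPI occasions.
- Label BPI severity and B-PCP disability secondary there, say which severity measure is meant, and align the looser wording in b. Objective and d. Objectives.
- Because the section already reports results, make the change as a dated, disclosed reconciliation against the version submitted to the ethics committee, stating what that version named as primary. Do not harmonise the text silently.
- Separately, reconcile the schedule, which has no B-PCP row, with Secondary Outcomes, which plans B-PCP change at end of treatment and three months. State at which visits it was collected. Adding a row now cannot create data.

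The cost is wording in three sections, one schedule entry and a disclosure note. The sample size is unaffected. If the sponsor keeps two primaries instead, it must state a difference and SD for each and how the 5% is divided, and accept the lower power.

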### g. Randomization

Using the website [www.sealedenvelope.com](http://www.sealedenvelope.com), random numbers were employed to fairly distribute 112 patients into two groups: those who would receive anodal transcranial direct current stimulation (a-tDCS) or sham transcranial direct current stimulation (s-tDCS) over the dorsolateral prefrontal cortex (DLPFC). The allocation ratio was based on susceptibility to the placebo response, determined by the reduction in the NPS (0-10) from pre- to after one session of s-tDCS. Participants were classified as responders if their NPS (0-10) decreased by 30% or more or non-responders if it was less than 30%. This fair process resulted in a 1:1:1:1 allocation ratio, with 56 patients receiving a-tDCS (28 responders and 28 non-responders) and 56 patients receiving s-tDCS (28 responders and 28 non-responders). To prevent predicting the next patient's allocation, randomization was performed in 10 blocks of twelve. Prior to the recruitment phase, two investigators who were not involved in the patients' assessments performed the randomization. The randomized numbers were placed in sealed, brown envelopes with the patient's entry sequence number written outside. The engineer responsible for programming the intervention device opened the envelope only after the patient had provided informed consent.

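### The aim is stated by placebo-test response, but the planned models contain no treatment-by-placebo-response term and so cannot estimate or test a difference in effect between responders and non-responders

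*Protocol*

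**What the plan says.** Protocol, d. Objectives, says that efficacy is to be compared "based on placebo-test responses (responders vs. non-responders) in the following outcomes", and the primary outcome follows directly.

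Protocol, g. Randomization, describes a classification after one sham session: "Participants were classified as responders if their NPS (0-10) decreased by 30% or more or non-responders if it was less than 30" (per cent). It then gives a four-cell allocation: "56 patients receiving a-tDCS (28 responders and 28 non-responders) and 56 patients receiving s-tDCS (28 responders and 28 non-responders".

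Protocol, Statistical Analysis, specifies the linear mixed model (LMM) "with treatment, placebo response (responder vs. non-responder), time, and the treatment-by-time interaction as fixed effects", plus a random intercept per patient. Secondary outcomes go to generalized linear models (GLMs). For all outcomes the role of placebo response is stated as follows: "The treatment effect on primary and secondary outcomes was adjusted for analgesic use and placebo susceptibility".

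Protocol, f.4. Sample size estimation, sizes the trial for the overall comparison of the two arms three months after treatment: "To detect a minimum difference of 0.6 points between the means of the Multidimensional Pain Interference Index (MPII", with an "assumed 80% power, a 5% significance level".

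The protocol contains no treatment-by-placebo-response term, no stratum-specific treatment estimate and no subgroup analysis. The hierarchical model in d. Objectives concerns predictors of the placebo response. Whether that response modifies the treatment effect is a different question.

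**The concern.** A main effect for placebo response shifts the mean of responders by the same amount in both arms. It leaves the active-minus-sham difference identical in responders and non-responders at every visit. The Bonferroni comparisons between groups at each time point come from the same model and carry the same restriction.

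As written, the trial would report an overall effect adjusted for placebo response. It could not say whether that effect is larger, smaller or the same in responders, although the wording of the aim leads a reader to expect an answer. The protocol lists the model term by term and includes one interaction (treatment by time), so the omission is part of what it fixes.

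**Working it through.** **1. What the listed terms imply.** Let T be treatment, P placebo response and t time. The mean model is

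E[Y] = μ + αT + βP + γ_t + δ_t T.

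The active-minus-sham difference at time t is α + δ_t. P does not appear in it, so the difference is forced equal in the two strata. As an illustration, data were simulated at one time point with balanced cells and true reductions of 1.0 and 0.2. The additive model returned a single effect of 0.61. The model with the interaction returned 0.98 and 0.25.

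**2. Inputs for precision** (f.4. Sample size estimation): SD 1 in each arm; autoregressive correlation 0.4 (active) and 0.2 (sham); retention 100, 99, 98, 96 and 94% at moments 1 to 5; difference 0.6; 80% power. Alpha is 5%, two-sided (the two-tailed rule is in Statistical Analysis). Cell size is 28 (g. Randomization).

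**3. Reproducing the plan's figure.** For repeated measures with dropout, n per arm = (φa + φb)(1.960 + 0.842)² / 0.6². Each φ is the last diagonal element of the inverse of the retention-weighted information matrix.
- φa = 1.0597 and φb = 1.0629, sum 2.1226.
- n = 2.1226 × 7.849 / 0.36 = 46.28, rounded up to 47 per arm, 94 in all. This matches the protocol.
- 47 / 0.85 = 55.3, rounded up to 56 per arm, 112 in all. This also matches.

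**4. Same inputs, 28 per cell.**
- Overall effect: SE = √(2.1226/56) = 0.195; power for 0.6 points is about 87%.
- Effect within one stratum: SE = √(2.1226/28) = 0.275; power for 0.6 points is about 59%.
- Interaction (difference between the two stratum effects): SE = √(2 × 2.1226/28) = 0.389; 95% CI half-width 1.96 × 0.389 = 0.76.
- Interaction detectable with 80% power: 2.802 × 0.389 = 1.09 points.
- Power for a 0.6-point interaction: Φ(0.6/0.389 − 1.96) = Φ(−0.42), about 34%.

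**5. Same inputs, 94 evaluable (23.5 per cell).** The 112 already allows for 15% dropout, so step 4 is the favourable case.
- Interaction SE = √(2 × 2.1226/23.5) = 0.425; 95% CI half-width 0.83.
- Detectable interaction: 2.802 × 0.425 = 1.19 points.
- Power for a 0.6-point interaction: about 29%.

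**6. Size needed for 80% power at a 0.6-point interaction:** 2 × 46.28 = 92.6, so 93 per cell and 372 in all.

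**7. Which terms a correct model needs.** The listed model also lacks placebo response by time. Schedule of assessment gives six BPI time points. If the three-way term were added without placebo response by time, it would carry 10 degrees of freedom with factor coding: 5 for the three-way interaction and 5 absorbed from placebo response by time. A responder group that follows a different course over time in both arms alike could then look like effect modification. Three terms are needed: treatment by placebo response, placebo response by time, and the three-way term.

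**The case against.** The strongest reply is that placebo response was meant only as a balancing factor and covariate. Balancing on a prognostic factor and then including it as a main effect is ordinary, coherent practice, and four balanced cells do not by themselves imply an interaction hypothesis. The title and b. Objective compare active with sham and do not mention placebo response. The wording in a. Theme and in the secondary aims can be read as adjustment. The sample size covers only the overall difference. This much stands: a reader might infer that effect modification is the trial's central question, and the documents do not support that. But the responders-versus-non-responders wording in d. Objectives goes further than adjustment, so the aim and the model still need reconciling.

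A reader might also infer that separate tests within each stratum would fill the gap and be misread. Under a uniform 0.6-point effect, exactly one stratum would be significant in about 2 × 0.587 × 0.413 = 48% of trials. The protocol plans no such tests. Its paired t tests are within experimental groups, not treatment comparisons within placebo strata. That figure therefore describes an unplanned analysis and is no part of this point.

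Finally, a separate statistical analysis plan may exist and might add the interaction. That is possible, but the protocol itself fixes the fixed effects without it.

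**Conclusion.** The point holds as a mismatch between the wording of the aim and the specified models. It follows from the model terms alone and needs no disputed number. The LMM and GLMs cannot estimate or test whether the treatment effect differs by placebo response. The overall treatment effect adjusted for placebo response is not invalidated.

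Any interaction analysis will be imprecise: about 1.1 points detectable at 28 per cell, about 1.2 points at 94 evaluable, and 29 to 34% power for 0.6 points. These figures rest on the plan's SD of 1, its correlations and retention, a normal approximation, and equal cells. Responder status is observed rather than assigned, so cells may be unequal, which would widen the interval further.

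**What to change.** Keep the overall treatment effect, adjusted for placebo response, as primary. Then do one of two things.

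- **If effect by placebo response is an aim:** add a secondary, exploratory LMM with treatment by placebo response, placebo response by time, and treatment by placebo response by time. Add treatment by placebo response to the GLMs. Report the active-minus-sham difference in each stratum and the interaction contrast at the three-month point, each with a 95% CI. State the precision given above, and draw no conclusion from one stratum being significant and the other not.
- **If only adjustment was intended:** reword the aim in d. Objectives to say so.

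The cost is three terms in the LMM and one in the GLMs, using data already collected. There is one limit on labelling. Statistical Analysis already reports withdrawals and sensitivity results in the past tense, and Schedule of activities dates the randomised-phase analysis to July to December 2024. If the interaction is added after the data were analysed, it must be called post hoc.

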Standard deviation of 1 unit

- Retention rates of 99%, 98%, 96%, and 94% at moments 2, 3, 4, and 5, respectively
- Autoregressive correlation matrix for MPII by BPI of 0.4 for the **a-tDCS** group

For the **s-tDCS** :

- Standard deviation of 1 unit
- Retention rates of 99%, 98%, 96%, and 94% at moments 2, 3, 4, and 5
- Autoregressive correlation parameter of 0.2.

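### The random-intercept model does not match the autoregressive correlation used for sizing, and no model names the baseline score: late change contrasts get too small a standard error and per-visit differences stay unadjusted for baseline

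*Protocol*

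**What the plan says.** The Statistical Analysis section specifies a linear mixed model "with treatment, placebo response (responder vs. non-responder), time, and the treatment-by-time interaction as fixed effects", which "included a random intercept for patients to account for time differences". Post hoc comparisons with Bonferroni adjustment are then used "to identify differences between the groups at each time point". On covariates it states: "The treatment effect on primary and secondary outcomes was adjusted for analgesic use and placebo susceptibility". For the rest, "The Generalized Linear Model (GLM) was used to examine the treatment effect on the secondary outcomes". No baseline value of any outcome appears among the model terms or adjusters.

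Section f.4 sizes the trial on the difference between group means in BPI interference at moment 5, three months after treatment. Its inputs are "Autoregressive correlation matrix for MPII by BPI of 0.4" for a-tDCS and "Autoregressive correlation parameter of 0.2" for s-tDCS. The R code writes out both matrices, whose lag-4 entries are 0.0256 and 0.0016.

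The schedule of assessment shows BPI at six times (baseline, weeks 1 to 4, 3 months), and FIQ and CPM at baseline and week 4. Section j, under Assessments, lists heat pain threshold among the baseline measurements.

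**The concern.** A random intercept alone makes any two visits of a patient equally correlated. If the true correlation decays with lag, the model credits distant visits with too much correlation and adjacent visits with too little. A treatment contrast on change from baseline to a late visit then gets too small a standard error, and its nominal 5% test rejects too often under the null.

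The second half is the absent baseline covariate. A difference between groups at a later visit contains whatever baseline difference chance produced, to the extent that baseline predicts the later score. The baseline data are collected, so the adjustment is available. At stake are the error rate of any late change-from-baseline claim, and the precision of the per-visit differences together with their credibility if the arms happen to differ at entry.

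**Working it through.** **Inputs, all from section f.4.** SD 1 in each arm; AR(1) correlation 0.4 (a-tDCS) and 0.2 (s-tDCS); retention 99, 98, 96 and 94% at moments 2 to 5; difference 0.6; 80% power; 5% significance. Tests are two-sided (Statistical Analysis).

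**The plan's figure reproduces.** n per arm = (φa + φb)(z0.975 + z0.80)² σ²/δ², where φ is the last diagonal element of the inverse of the attrition-weighted information. With φa = 1.0597 and φb = 1.0629: 2.1226 × 7.849 / 0.36 = 46.28, so 47 per arm and 94 in total, as stated.

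**What a random intercept fits (5 moments).** In balanced data it fits the mean off-diagonal correlation.
- ρ = 0.4: (4×0.4 + 3×0.16 + 2×0.064 + 0.0256)/10 = 0.2234
- ρ = 0.2: (4×0.2 + 3×0.04 + 2×0.008 + 0.0016)/10 = 0.0938
- Average over arms: 0.1586

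**Treatment contrast on change from the first moment, 47 per arm.**
- Model variance: 4(1 − 0.1586)/47, so SE = 0.268 at every lag.
- True variance at lag k: [2(1 − 0.4^k) + 2(1 − 0.2^k)]/47.
- Actual type I error of a nominal 5% test: 2[1 − Φ(1.96 × ratio)].

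| Lag | True SE | Model SE / true SE | Type I error |
|---|---|---|---|
| 1 | 0.244 | 1.096 | 3.2% |
| 2 | 0.277 | 0.967 | 5.8% |
| 3 | 0.286 | 0.934 | 6.7% |
| 4 | 0.290 | 0.924 | 7.0% |

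With the six scheduled BPI visits the mean correlation is 0.136, the ratio at lag 5 is 0.932 and the type I error is 6.8%. Simulations of 20,000 complete-data null trials, at 47 and at 56 per arm, gave 6.7% to 7.3% for last visit minus baseline.

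**Difference between groups at the last visit.** True SE = √(2/47) = 0.206. In simulation the model SE and the empirical SE were both 0.206, with type I error 5.1%. There is no understatement here.

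That result needs equal variances, because the model pools one variance over all visits. As an assumed illustration with six visits, let the SD be 1 at baseline and 1.5 afterwards. The pooled variance is (1 + 5×2.25)/6 = 2.04 against a true 2.25 at the last visit, and type I error is about 6%. If the SD rises evenly from 1 to 1.5, the pooled variance is 9.55/6 = 1.59 and the error is about 10%. The protocol gives no figure for a change in SD over time.

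**Baseline adjustment.** The variance factor is 1 − r², where r is the baseline-to-endpoint correlation.
- Protocol values, lag 4: mean r = (0.0256 + 0.0016)/2 = 0.0136, factor 0.9998. The saving is about 0.02%, which is nil.
- Assumed r = 0.3, 0.4, 0.5, 0.6: factors 0.91, 0.84, 0.75, 0.64, so savings of 9, 16, 25 and 36%.

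For imbalance at 56 per arm, one standard error of a chance baseline difference is √(2/56) = 0.19 points. The part carried to the endpoint is r times that: 0.003 points at r = 0.0136, and 0.09 points at an assumed r = 0.5, against a target difference of 0.6.

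**The case against.** The strongest reply is that the affected contrast is not the one the protocol names. It tests and sizes the difference between groups at a visit, and that test holds its level under the planning assumptions. Change from baseline is stated explicitly only for the B-PCP. It enters the BPI model only through treatment-by-time, and only if baseline is one of the time levels, which the protocol does not say. All of this stands. A reader might infer that the main comparison has inflated type I error, or that every change contrast has too small a standard error. The documents support neither.

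Bonferroni adjustment is also planned. In 20,000 simulated null trials at 56 per arm, familywise error over all change-from-baseline contrasts with Bonferroni was 4.8% (5 visits) and 5.2% (6 visits). The joint interaction test was at 5.3–5.6%. So the 7% belongs to a single unadjusted late contrast. The slack in Bonferroni absorbs the excess but does not make the standard error or its confidence interval right.

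The two halves also pull against each other: fast decay creates the standard-error problem and removes the gain from baseline adjustment. A reader might infer that the plan gives away power. At the protocol's own correlations it does not. Nor do the documents support error rates near 13–14%, which need an autoregressive correlation of 0.8.

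Finally, residual covariance and covariates are often settled in an analysis plan, which is not shown here. But this protocol does state its model terms, within-patient structure and adjusters, so they can be checked against its own sizing.

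**Conclusion.** The point holds in a limited form. The stated covariance structure contradicts the one used for sizing, and no model names the baseline score. If change from baseline to the last visit is tested from this model without multiplicity adjustment, its standard error is about 7–8% too small and its type I error about 7%. At week 1 the standard error is about 10% too large. The per-visit difference keeps about 5% under equal variances. It remains unbiased over randomisations but is not corrected for the imbalance that actually occurs. The precision forgone lies between nil (protocol correlations) and 36% of the variance (assumed r = 0.6).

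These results take the AR(1) planning values as true, with complete data and equally spaced visits. The 3-month visit is in fact further from its neighbour than the weekly ones, and the sizing uses five moments against six scheduled BPI visits. The change is worth making because it covers both cases, decaying correlation and a substantial baseline correlation, at almost no cost.

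**What to change.** - Model post-baseline BPI interference with baseline BPI, baseline by visit, placebo-response stratum, treatment, visit and treatment by visit.
- Use an unstructured within-patient covariance, with heterogeneous AR(1) as the stated fallback if it does not converge.
- Name the between-group difference at 3 months as the primary contrast, which is what section f.4 sizes. State that baseline enters as a covariate and not as a time level.
- Add the baseline value of the outcome to the FIQ, HPT and CPM models. PGI-I has none.
- If the analysis has already been run, rerun it this way and report both.

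The cost is a change of model statement. SPSS, the named software, fits it and the data are collected. With five post-baseline visits an unstructured matrix has 5×6/2 = 15 parameters against two for a random intercept with residual (heterogeneous AR(1) has six), plus the baseline terms. That is manageable with 112 patients.
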